### Data management

The study will adhere to the Data Protection Act (1998) and to the General Data Protection Regulation (GDPR). Data from this study will be pseudonymised and stored in password-protected computer systems or institutional secure drivers accessible only by the members of each local research team in order to guarantee confidentiality to patients. Paper forms will be stored in locked filing cabinets. Data will be kept at Sheffield Hallam University for a 7-year period following the study completion to allow the study team to answer all the research questions.

All data documents will be kept in secured and continuously monitored buildings. All study materials will remain in this location for data entry and storage. Participant names will not be used to identify any data. Instead, participants will be assigned a study identification number (e.g. SSc001) in order to pseudonymise their information and thus all the related collected data. Publications will not contain identifiable personal data. Furthermore, only local research principal investigators will have access to personal patient data during the project, while data will be analysed locally. Following data collection and local data analysis, all research centres will securely (e.g. via drivers) transfer the data to Sheffield Hallam University to perform the statistical analysis. All centres will have digital secure access to the final aggregated large database.

### Data monitoring

The data monitoring committee (DMC) will be comprised of the research manager and chief investigator of the leading research centre (i.e. Sheffield Hallam University) due to the low risk of the intervention. The conduct of the study will be overlooked on a daily basis by the chief investigator [name] at Sheffield Hallam University. Research meetings will be held between all members of the research team once monthly to discuss further progress and set targets. The DMC is independent from the sponsor and has no competing interests.

Moreover, a designated member of the research team will conduct audit trials to the study’s centres to explore whether the study is running according to the SOP at regular intervals. This audit will be run independently of the sponsor.

### Safety monitoring

We will record all serious adverse events (as defined below), as well as all non-serious adverse events that are deemed to be related to participation in the research, during the period between the provision of informed consent through to 6 months after randomisation.

Serious adverse events are defined as any untoward medical occurrence that either results in death, is life-threatening (i.e. the patient is at risk of death at the time of the event occurring), requires unplanned admissions to emergency hospitalisations or prolonged hospitalisation (deemed to be where a patient’s stay is longer than expected, e.g. patient is operated on as a day case but remains in hospital overnight) or results in persistent or significant disability or incapacitation.

A non-serious event in the context of this trial will be any untoward medical occurrence to the participant that is related to the patients’ involvement in the study but does not fulfil any of the serious adverse event criteria.

### Statistical analysis

Data analysis will be performed using SPSS software (IBM SPSS, New York, USA) and will be presented as mean ± SD. Normal distribution of the data and homogeneity of variances will be tested using the Shapiro-Wilk and Levene’s test, respectively. The comparison between the two groups for pain and fatigue (primary outcomes) as well as NVC, functional capacity tests, and V̇O_2peak_ test (secondary outcomes) will be performed through independent *t*-tests, Wilcoxon, chi-squared, Mann-Whitney *U*, and Kruskal-Wallis tests. Mixed model ANCOVA will also be performed to test the differences both within and between subject effects across time [three measurements: baseline, 12 weeks (primary time-point), and 24 weeks post-baseline]. Effect sizes (Cohen’s *d*) will be calculated wherever the results will be statistically significant with 0.2, 0.5, and 0.8 representing small, medium, and large effects respectively [36]. Statistical significance will be set at *p* ≤ 0.05. Data analysis will commence at the end of the 2nd data collection post-baseline (i.e. 12 weeks).

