## Methods

### Study design

The CESPF (The effects of a combined supervised exercise programme on pain and fatigue in SSc) study is a multi-centre (*n*=6) randomised (1:1 ratio), parallel group, superiority, controlled clinical trial. One hundred and eighty SSc will be recruited across six research institutions (Sheffield Hallam University, Sheffield, UK; Karolinska Institutet, Stockholm, Sweden; Rigshospitalet Hospital, Copenhagen, Denmark; Leiden University Medical Center, Leiden, Netherlands; Aristotle University, Thessaloniki, Greece; University of Campania L. Vanvitelli, Naples, Italy) and will be randomly assigned via stratified block randomisation remotely by an independent statistician to either group A (combined exercise) or group B (control group). Both groups will continue receiving their usual medical as well as non-pharmacological treatment (if applicable) throughout the study. Patients will be followed for 6 months following randomisation (Fig. 1). Assessors will be blinded regarding the allocated treatments. The study’s protocol and registration have been published in ClinicalTrials.gov (NCT number: NCT05234671) January 02, 2022. The trial is sponsored by the Foundation for Research in Rheumatology, and medical (where applicable) or non-medical ethical approval has been granted by each research centre locally. The reporting of this study protocol is done according to the Standard Protocol Items Recommendations for Interventional trials (SPIRIT).

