### Group randomisation

Following VISIT 1, participants will be randomised remotely (to ensure allocation and concealment) into groups A (combined exercise) and B (control group), using a computer programme (nQuery Advisor 6.0, Statistical Solutions, Ireland) to generate stratified block-randomisation (by research centre, SSc-type, disease duration and severity), by an independent statistician. Each participant will be allocated a unique trial number across all sites (e.g. SSc001) that will remain with them throughout the study.

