#### Sample size

The primary outcome was the RP pain. For our calculations, we used commercial software (G*Power 3.1.7, HHU of Düsseldorf) by using data from two studies that examined the exercise training effects on SSc-QoL [35, 37]. Based on those calculations, we will need no more than 90 patients in each group (180 in total) to detect a difference in RP’s pain at 3 months (significance level = 0.05; power =80%) accounting also for an estimated 15% dropout and 5% site effect.

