### Practical issues

The current study is expected to overcome some practical issues that might appear as a result of the multi-centre collaboration. Namely, local ethical approvals were the first practical issue that has now been overcome and recruitment has been initiated in all European centres. Completing recruitment on time is the next challenge of this multi-centre trial; nevertheless, all centres and investigators have got the experience and the appropriate number of people with SSc to contribute effectively to the recruitment target (i.e. approximately 30 participants per centre). Another practical issue is the standardisation of the baseline and follow-up assessments across all centres. The standardisation has been secured by creating a standard operating procedures manual which is strictly followed by all research centres and investigators.

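### Patients are randomised within strata of centre, SSc type, disease duration and severity, but the named between-group tests for pain and fatigue cannot use these factors, so an unadjusted 12-week comparison is conservative and forgoes some power

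*Protocol article*

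**What the plan says.** Study design describes a "randomised (1:1 ratio), parallel group, superiority, controlled clinical trial" in six institutions, and Practical issues expects "approximately 30 participants per centre". Group randomisation uses a computer programme "to generate stratified block-randomisation (by research centre, SSc-type, disease duration and severity), by an independent statistician".

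Sample size gives the total: "we will need no more than 90 patients in each group (180 in total) to detect a difference in RP’s pain at 3 months", at a 0.05 significance level and 80% power, "accounting also for an estimated 15% dropout and 5% site effect". It gives no effect size or standard deviation and does not define the site effect.

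Statistical analysis introduces the tests with "The comparison between the two groups for pain and fatigue (primary outcomes) as well as NVC, functional capacity tests" and lists independent t-tests, Wilcoxon, chi-squared, Mann-Whitney U and Kruskal-Wallis tests. It then adds a mixed model ANCOVA over baseline, 12 weeks (the primary time-point) and 24 weeks, described only by within- and between-subject effects across time. Neither centre nor any other stratification factor is named in any analysis.

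The Discussion states that pain and fatigue are both associated with more severe disease.

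**The concern.** Stratified allocation makes the arms alike on the stratification factors. If those factors predict the outcome, the arm difference varies less from trial to trial than it would under simple randomisation. A two-sample test that ignores them still counts the between-stratum variation as error, so its standard error is too large, its p-value too high and its confidence interval too wide.

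The protocol gives its own grounds for expecting this. Severity is a stratum, and the Discussion ties both primary outcomes to it. The sample size also allows for a site effect. Yet the tests named for the primary comparison have no place for either factor. At stake is precision on pain and fatigue that the randomisation makes available and the named tests do not use.

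**Working it through.** **Inputs from the protocol article.** 90 per group; 80% power; alpha 0.05 (sidedness not stated, two-sided assumed); 15% dropout; 5% site effect; six centres of about 30; four stratification factors.

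**Assumptions.** R², the share of 12-week outcome variance explained by the strata, is not given, so a range of 0.05 to 0.30 is used. The low end matches one possible reading of the site effect, as a variance share. The number of levels per factor and the block size are also not given.

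**The plan's own figure.** The 90 per group cannot be reproduced without an effect size, only back-solved. Evaluable patients per arm: 90 × 0.85 × 0.95 = 72.7. Standardised effect: d = (1.96 + 0.84) × √(2/72.7) ≈ 0.465. Forward, d = 0.47 needs 72 per arm, and 72/0.85/0.95 = 89.2, rounded up to 90. So 90 is consistent with d of about 0.47.

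**Formulas (large sample, strata perfectly balanced, outcome SD = 1, n evaluable per arm).** The true variance of the arm difference is 2(1−R²)/n, but the unadjusted t-test uses 2/n. With the effect fixed at 80% nominal power, the standardised difference is 1.96 + 0.84 = 2.80, so the results do not depend on n:
- standard error ratio = 1/√(1−R²)
- true type I error, unadjusted = 2[1 − Φ(1.96/√(1−R²))]
- power, unadjusted = Φ((2.80 − 1.96)/√(1−R²))
- power, adjusted = Φ(2.80/√(1−R²) − 1.96)

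| R² | SE too large by | Type I error, unadjusted | Power, unadjusted | Power, adjusted | Difference (points) |
|---|---|---|---|---|---|
| 0.05 | 2.6% | 4.4% | 80.6% | 82.0% | 1.4 |
| 0.10 | 5.4% | 3.9% | 81.3% | 84.0% | 2.7 |
| 0.20 | 11.8% | 2.8% | 82.7% | 88.0% | 5.3 |
| 0.30 | 19.5% | 1.9% | 84.3% | 91.8% | 7.5 |

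**Imperfect balance.** If SSc type, duration and severity each have two levels, there are 6 × 2 × 2 × 2 = 48 cells for 180 patients, or 3.75 per cell, so many blocks stay incomplete. The table is therefore the extreme case for type I error. Simulation with six centres of 30, three binary strata, blocks of 4 (assumed) and 15% dropout gives, unadjusted against adjusted:
- R² 0.20: type I error 4.0% against 5.1%; power 82% against 87%.
- R² 0.30: type I error 2.9% against 5.2%; power 82% against 91%.

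**Centre only.** Simulation with six centres of 24, balanced within centre:
- Intraclass correlation 0.05: null rejection 4.6% against 5.0%; power 80.2% against 81.3%.
- Intraclass correlation 0.20: null rejection 3.1% against 4.7%; power 83.3% against 87.7%.

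Across these calculations, the adjusted analysis gains about 1 point at the low end and about 9 at the high end. All power figures are for the back-solved effect.

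**The case against.** The strongest reply is that the article also names a mixed model ANCOVA. Such a model has covariates by definition, and listing them is normally left to an analysis plan, which is not shown. This stands for that model: the text does not put the strata in, but it does not rule them out. A reader might infer that the trial will ignore its strata in every analysis; the document does not support that. The point rests on the t-tests, rank tests and chi-squared tests, which the article itself names for the primary comparison.

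Second, stable stratum differences largely cancel in a change from baseline and are largely absorbed when baseline is a covariate. This also stands. The section does not say whether the t-tests use 12-week values or changes; the figures above assume 12-week values. In simulation with the same stratified layout, d = 0.46 and an assumed baseline-to-12-week correlation of 0.6 (not in the documents), power with baseline alone against baseline plus strata was 94.2% against 94.0% at R² 0.05, 93.8% against 94.6% at 0.20, and 94.7% against 96.2% at 0.30. Once baseline is in the model, the strata add at most about 1.5 points.

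Third, no stated operating characteristic fails. A reader might infer that the trial drops below its planned power or that its false-positive risk rises. Neither follows: at the back-solved effect the unadjusted test keeps 80% or slightly more, and its type I error is below 5%. The loss is relative to a better analysis of the same data.

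Fourth, a reader might infer that the patients added for the site effect are wasted if site is not modelled. That is wrong. Extra patients raise the power of any test, and enlarging the sample is a natural allowance when site variance stays in the error term.

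**Conclusion.** The point holds in a limited form. The tests named for the primary between-group comparison do not use the factors that govern allocation, and the ANCOVA description does not name them. Since the protocol itself links pain and fatigue to severity, an unadjusted 12-week comparison would be conservative.

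The direction is certain wherever the strata predict the outcome; the size is not. At R² 0.05, type I error is about 4.4% and about 1 power point is forgone. At R² 0.30, type I error is 2–3% and about 7 to 9 points are forgone. The upper half of that range has no source in the documents, and the whole range assumes 12-week values analysed without baseline. This is a worthwhile, nearly free improvement to the analysis, not a flaw that invalidates the trial.

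**What to change.** In Statistical analysis, define the primary between-arm comparison of pain and of fatigue at 12 weeks as a linear or mixed model with the baseline value, research centre, SSc type, disease duration and severity as main effects. Report the adjusted difference with its 95% confidence interval. Use main effects rather than the full cross-classification, because the cells are too small. Treat the unadjusted tests as supportive; where a rank test is needed, use one stratified by centre (van Elteren).

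The change is to wording only, and should be fixed before outcome data are examined by arm, since analysis is due to start once the 12-week data are collected. All the factors and the baseline value are already collected, so no new data are needed. With one term each for SSc type, duration, severity and baseline, the cost is 5 + 1 + 1 + 1 + 1 = 9 degrees of freedom, out of about 150 evaluable patients (180 × 0.85 = 153).

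### No single test is named for the primary 12-week comparison: the plan lists tests unadjusted for baseline and a mixed ANCOVA that treats baseline as a repeated outcome

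*Protocol article*

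**What the plan says.** All of the following is in the protocol article.

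- **Scope of the list (Statistical analysis).** One sentence covers primary and secondary outcomes together: "The comparison between the two groups for pain and fatigue (primary outcomes) as well as NVC, functional capacity tests" and the peak oxygen uptake test. These comparisons "will be performed through independent *t*-tests, Wilcoxon, chi-squared, Mann-Whitney *U*, and Kruskal-Wallis tests".
- **Assumption checks.** "Normal distribution of the data and homogeneity of variances will be tested using the Shapiro-Wilk and Levene’s test, respectively". No rule links the results of these checks to the choice of test.
- **Additional model.** "Mixed model ANCOVA will also be performed to test the differences both within and between subject effects across time", with "three measurements: baseline, 12 weeks (primary time-point), and 24 weeks post-baseline". Baseline is therefore one of the repeated measurements. The label naming 12 weeks as primary stands only in this description of the model.
- **Threshold.** "Statistical significance will be set at *p* ≤ 0.05".
- **Randomisation (Group randomisation).** The scheme is "stratified block-randomisation (by research centre, SSc-type, disease duration and severity"). None of these factors appears in the analysis text.
- **Power (Sample size).** The trial is powered for Raynaud's pain at 3 months with 90 patients per group ("significance level = 0.05; power =80"%), allowing 15% for dropout and 5% for a site effect. No effect size or standard deviation is given.

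**The concern.** The primary scores are two pain scales and a fatigue score, each compared between two parallel arms. For them the plan offers several analyses and does not rank them. The listed tests do not adjust for baseline, and they carry no time point.

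The mixed model has two overall tests. Its group main effect averages over a visit at which randomisation makes the expected difference zero. Its group-by-time test has 2 degrees of freedom and asks whether the arms differ in profile over three visits. Neither is the 12-week difference on which the trial is powered.

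Two things are at stake. Precision available from data already collected may be lost. The p-value that answers the main question can also be chosen after the results are seen.

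**Working it through.** **1. Back-solving the planned effect.** The sample size cannot be reproduced without an effect size, so I solve for it. Removing 15% and 5% together leaves 90 × 0.80 = 72 per arm; removing them in turn leaves 90 × 0.85 × 0.95 = 72.7. For a two-sided 5% test (sidedness is not stated) with 80% power:

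d = (1.960 + 0.842) × √(2/72) = 2.802 × 0.1667 = 0.467.

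Removing dropout alone leaves 76.5 per arm and gives d = 0.453. I use 72 and 0.467 as assumptions. I also assume equal correlation ρ between visits; its value is not stated, so I show 0.3, 0.5 and 0.7.

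**2. Power of the 12-week comparison.** The unadjusted test has 80.0% by construction. Baseline-adjusted ANCOVA multiplies the residual SD by √(1 − ρ²), so power = Φ(2.802/√(1 − ρ²) − 1.960).

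| ρ | √(1 − ρ²) | Power, ANCOVA | Gain over unadjusted | Evaluable n per arm for 80% |
|---|---|---|---|---|
| 0.3 | 0.954 | 83.6% | 3.6 points | 66 |
| 0.5 | 0.866 | 89.9% | 9.9 points | 54 |
| 0.7 | 0.714 | 97.5% | 17.5 points | 37 |

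**3. Group main effect over three visits.** If the 24-week effect is a fraction f of the 12-week effect, the averaged effect is (0 + d + f·d)/3 and the SD of a patient's mean is √((1 + 2ρ)/3). At ρ = 0.5 this SD is 0.816.

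- Effect persists (f = 1): Φ(2.802 × 0.667/0.816 − 1.960) = 62.8%.
- Effect halves (f = 0.5): Φ(2.802 × 0.5/0.816 − 1.960) = 40.3%.
- Effect vanishes (f = 0): Φ(2.802 × 0.333/0.816 − 1.960) = 20.7%.

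**4. Overall group-by-time test.** This is a chi-square test with 2 degrees of freedom. Under equal correlation the noncentrality is 2.802² × 2(1 − f + f²)/(3(1 − ρ)). At ρ = 0.5 this is 10.5 for f = 1 or f = 0 (power 83.4%) and 7.85 for f = 0.5 (power 70.9%). It can exceed the unadjusted test, but it stays below the 89.9% of ANCOVA. It also gives the same power whether the effect persists or vanishes at 24 weeks, which shows that it does not target 12 weeks.

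**5. Type I error from choosing among analyses.** I simulated 10,000 null trials with normal data, 72 per arm and ρ = 0.5.

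| What may carry the claim for one outcome | Type I error |
|---|---|
| Better of t-test and Mann-Whitney at 12 weeks | about 6% |
| Best of t-test, Mann-Whitney and baseline-adjusted ANCOVA at 12 weeks | about 8% |
| Best of t-test, Mann-Whitney, group main effect and group-by-time test | 12 to 13% |
| Shapiro-Wilk decides between t-test and Mann-Whitney | about 5% |

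**6. The list itself.** Kruskal-Wallis with two groups is the Mann-Whitney test again: on one simulated data set both gave p = 0.01416. Chi-squared suits the categorical capillaroscopy findings, not a continuous score. Wilcoxon, listed apart from Mann-Whitney, may mean the paired test, which does not compare arms; the text does not say.

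**The case against.** The strongest reply is that the listed tests are legitimate. An unadjusted comparison in a randomised trial is unbiased, and leaving out stratification factors tends to make it conservative. The sentence covers categorical capillaroscopy outcomes as well as scores, which explains the mixed list. A model called ANCOVA implies covariates, and a condensed article may leave their names to a fuller document.

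Much of this stands, and it rules out some stronger readings that a reader might infer:

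- **That nothing planned can isolate the 12-week difference.** A t-test or Mann-Whitney test at 12 weeks would do so, and a contrast could be drawn from the mixed model. The fault is that none is named as primary.
- **That the listed tests are invalid for two arms.** Kruskal-Wallis is redundant, not wrong. The text does not say that chi-squared will be applied to pain or fatigue, and reading Wilcoxon as the paired test is an inference.
- **That baseline goes unused.** A group-by-time contrast uses it, though less efficiently than ANCOVA.
- **That the type I error is 12%.** That needs the main effect or the interaction also to carry the claim, which the article does not say. If the normality test were the declared selection rule, the error would stay near 5%.

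What the reply does not answer is that the article is not silent here. It commits to a set of analyses for the primary outcomes without ranking them and places baseline among the outcomes of the model. A later document that names one adjusted contrast would replace this text rather than complete it.

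**Conclusion.** The point holds: the primary comparison is badly fixed. No analysis is identified as giving the primary 12-week result, no covariate is named, and the model's two overall tests address other questions.

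The size is conditional. The gain from baseline adjustment runs from about 4 to about 17 power points over correlations of 0.3 to 0.7. The type I error from free choice among 12-week tests is about 6 to 8% per outcome, and 12 to 13% is the worst case. These figures rest on a back-solved effect of about 0.47, 72 evaluable patients per arm, equal correlation between visits and normal data, none of which the article states. The low power of the three-visit main effect matters only if that effect were used for the primary claim.

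This should be fixed. It does not make the trial invalid, because an unadjusted 12-week comparison would still be a sound, if less precise, answer.

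**What to change.** For each primary score, name one primary analysis: the group difference at 12 weeks with its 95% CI. Take it either from an ANCOVA of the 12-week score or from a mixed model of the 12- and 24-week scores with group, visit and their interaction. In both, enter the baseline score, centre, SSc type, disease duration and severity as covariates, and do not treat baseline as an outcome.

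Keep Mann-Whitney as a sensitivity analysis and chi-squared for the categorical capillaroscopy outcomes. Drop Kruskal-Wallis, and say what Wilcoxon is for or remove it.

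This changes wording only. It needs no new patients or data and runs in the planned software. The cost is a few degrees of freedom for the covariates (five for six centres, plus those for the other factors). Because analysis is due to begin once the 12-week data are collected, the change should be recorded before outcomes are seen by arm.

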**Discussion:**

Data from this multi-centre research clinical trial will primarily be used to establish the effectiveness of a combined exercise protocol to improve pain and fatigue in SSc. In parallel, this study will be the first to explore the effects of long-term exercise on potential microvascular alterations assessed via NVC. Overall, this study will provide sufficient data to inform current clinical practice guidelines and may lead to an improvement of QoL for patients with SSc.

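### Cohen's d is tied to statistical significance, so the reported values are biased upward and non-significant outcomes get no planned effect estimate

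*Protocol article*

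**What the plan says.** All of the relevant text is in the Statistical analysis section of the protocol article.

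- Data "will be presented as mean ± SD". No significance condition is attached to this.
- The primary and secondary outcomes are compared between groups with t-tests, rank tests and chi-squared tests. A mixed model ANCOVA is also planned over three measurements: baseline, "12 weeks (primary time-point), and 24 weeks post-baseline".
- Effect sizes (Cohen's d) "will be calculated wherever the results will be statistically significant", read against "0.2, 0.5, and 0.8 representing small, medium, and large effects respectively".
- "Statistical significance will be set at" p ≤ 0.05.

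The section names no other between-group effect measure. The Discussion part of the abstract says that "this study will provide sufficient data to inform current clinical practice guidelines".

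**The concern.** The Cohen's d sentence is a positive instruction, not a gap. It makes calculation of the one named effect measure depend on the p-value. Two things follow.

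First, an estimate that is shown only when it is large enough to be significant is on average too large. The lower the power for an outcome, the stronger this effect. The sample size was set for Raynaud's pain, so power for fatigue, overall pain and the secondary outcomes is not established.

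Second, an outcome that misses the threshold has no planned effect estimate, even if it is one of the primary outcomes. A trial meant to inform guidelines needs the size and precision of each effect, and most of all when the result is not significant.

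**Working it through.** **Inputs from the article.** 90 patients per group, 1:1 allocation, and an allowance of 15% for dropout and 5% for a site effect (Study design; Sample size). Alpha and power are given as "significance level = 0.05; power =80"%. The threshold and the bands for d are quoted above.

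**Assumptions.** Tests are two-sided (not stated). The outcome is continuous and compared by a two-sample t-test. Evaluable numbers are 72 per arm (90 × 0.80), with 90 per arm as the upper end. The true effects are assumed, because the article gives no difference, SD or effect size.

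**The plan's own figure.** For that reason the 90 per group cannot be reproduced forward. Solved backwards, the detectable effect is d = √(2/n) × (1.960 + 0.842).

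- n = 72: 0.1667 × 2.802 = 0.467.
- n = 76.5 (dropout only): 0.453.
- n = 90 (no allowance): 0.418.

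**Smallest d that can be significant.** This is t(0.975, 2n − 2) × √(2/n).

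- n = 72: 1.977 × 0.1667 = 0.329.
- n = 90: 1.973 × 0.1491 = 0.294.

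An observed d near 0.2, the article's benchmark for a small effect, therefore falls below what this test could ever release for reporting.

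**Mean d with and without selection.** 400,000 simulated t statistics per scenario, with d̂ = t × √(2/n), at 72 per arm:

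| True d | Power | Mean d̂, all | Mean d̂, p ≤ 0.05 | Ratio to truth |
|---|---|---|---|---|
| 0.10 | 9% | 0.101 | 0.363 | 3.6 |
| 0.20 | 22% | 0.201 | 0.425 | 2.1 |
| 0.30 | 43% | 0.302 | 0.455 | 1.5 |
| 0.40 | 66% | 0.402 | 0.495 | 1.24 |
| 0.467 | 80% | 0.470 | 0.530 | 1.13 |
| 0.60 | 95% | 0.603 | 0.623 | 1.04 |
| 0.80 | 99.7% | 0.804 | 0.806 | 1.01 |

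With 90 per arm the ratios are 1.93 at 0.20, 1.39 at 0.30, 1.08 at 0.467 and 1.00 at 0.80.

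**Check by formula at d = 0.30, n = 72.** With SE = 0.1667, d/SE = 1.80 and critical value 1.977, the mean given significance is about d + SE × φ(1.977 − 1.80)/power = 0.30 + 0.1667 × 0.393/0.430 = 0.452. This agrees with the simulated 0.455. The opposite tail is negligible here.

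**Share without a d.** At a true d of 0.30, 1 − 0.434 = 57% of such outcomes would have no Cohen's d calculated.

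**The case against.** The strongest reply is that a reader might infer that null outcomes carry no estimate at all and cannot be interpreted. The article does not support that. Means and SDs are promised for the data without reference to significance. From these and the group sizes, anyone can derive an unadjusted difference, its confidence interval and d for a continuous outcome. This stands. What is lost is a planned estimate. The group summaries do not give the ANCOVA-adjusted difference or its interval, and they serve skewed or categorical outcomes poorly.

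A reader might also infer that the trial's published effects are inflated in general. That is too broad as well. The selection acts on the printed d values, not on the group means, and nothing says that non-significant outcomes will go unreported. The inflation is modest at 80% power and almost nil for large effects.

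A third reply is that this is a condensed article and that confidence intervals are commonly left to an analysis plan, which is not shown. This too is fair. The absence of an interval is not itself the point, and the sentence does not forbid other estimates. The conditional rule for d, however, is stated in the article and can be judged as it stands.

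**Conclusion.** The point holds in a limited form. The rule ties Cohen's d to p ≤ 0.05, which biases the reported d values upward and leaves non-significant outcomes without a planned effect estimate.

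The bias is about 13% at the effect that 72 per arm would detect with 80% power, about twofold at a true d of 0.20, and about 1% at 0.80. These sizes rest on assumed true effects, on 72 evaluable per arm and on a two-sided t-test. With 90 per arm they are somewhat smaller. They do not cover categorical or ordinal outcomes. Significance from the mixed model ANCOVA could release a smaller d than the t-test limit of 0.29 to 0.33.

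The hypothesis tests and the sample size are not affected. It should be corrected because the planned effect reporting is selective by design and the correction is simple.

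**What to change.** Delete the significance condition. State instead that, for every primary and secondary outcome, the between-group effect at 12 and 24 weeks will be reported with its 95% confidence interval whatever the p-value.

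- For continuous outcomes, use the mean difference from the planned mixed model ANCOVA, with Cohen's d alongside if wanted.
- For categorical or ordinal nailfold videocapillaroscopy outcomes, such as the scleroderma pattern or the presence of giant capillaries, use a suitable measure such as a risk difference or an odds ratio. A standardised mean difference does not fit these.

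The cost is slightly more reporting work. No new data are needed and the sample size does not change.
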